### Secondary outcomes

#### Subjective knee function

The PROMs and the specific time points of measurement are presented in Table 1.The Knee injury and Osteoarthritis Outcome Score (KOOS) [40],The International Knee Documentation Committee Subjective Knee Form (IKDC-SKF) [41],The Physical Activity Scale (PAS) [42],The the EuroQol 5-Dimension score (EQ-5D) [43],The Tegner Activity Scale [29],The Anterior Cruciate Ligament Return to Sports after Injury (ACL-RSI) [44],The Werner anterior knee pain (AKP) score [45],The Kartus anterior knee pain score [46]Graft site morbidity questionsReturn to Sports questionnaire (Table 2)

All scores that will be used have either originally been created or translated to Swedish [47, 48].

### Objective knee function

#### Knee joint examination

All clinical examination will be performed by one of the four experienced orthopedic knee surgeons participating in the study. The knee examination will assess knee ROM using a goniometer [49] and knee joint effusion (circumference of the joint using a measuring tape centered at the center of the patella) [50], anterior knee laxity with the knee in 20–30 ^o^ flexion (Lachman’s test), rotational laxity using the pivot shift test.

#### Graft site morbidity

Graft site morbidity will be assessed using two dichotomous (yes/no) questions. The first question will determine whether participants experience reduced sensation around the surgical site. If they answer 'yes,' the affected area will be measured in cm^2^. The second question will assess whether participants experience pain or discomfort at the surgical site.

#### Functional knee testing

To assess functional outcomes after ACL-R, isokinetic muscle strength testing and two single-legged hop (one-leg hop for distance and cross over hop) tests will be used [51]. Following a 10 min self-paced warm up in a stationary cycle ergometer, patients will perform the isokinetic strength tests and subsequently the hop tests.

The limb symmetry indexes (LSIs) of the peak extension and flexion torque and single-leg-hop tests are calculated as [involved limb/uninvolved limb × 100] for each test. For isokinetic strength and single-leg hop tests, symmetrical performance is defined as achieving at least 90% of the contralateral leg’s performance (LSI ≥ 90%) [31, 32]. Patients who achieve an LSI ≥ 90% in all four tests (isokinetic quadriceps strength, isokinetic hamstring strength, and single-leg hop test) are considered to have restored symmetrical knee function [31].

#### Isokinetic muscle strength testing

Isokinetic testing will be performed using the Biodex System 3 dynamometer (Biodex Medical Systems, Shirley, New York, USA) at follow-up time outlined in Table 1 [52]. The test will be conducted within a ROM from 90° to 0° of knee flexion, starting with the uninjured knee. The testing procedure will be verbally explained to participants, and they will be allowed two to three practice trials to familiarize themselves with each part of the protocol. Concentric knee extension and flexion torque will be measured bilaterally at 90°/s (5 test repetitions) and 240°/s (10 test repetitions), and isokinetic eccentric knee extension and flexion torque will be measured at 90°/s (5 test repetitions), according to the clinic’s previously published standard routine [26]. Standardized, verbal encouragement is provided throughout the test, and the peak extension and flexion torque values (highest recorded torque) are documented.

#### Hop testing

Hop performance will be assessed by the Single-Leg Hop test for Distance and the Crossover Hop test for Distance [51]. The Single-Leg Hop test for Distance is performed by standing on one leg and jumping straight ahead as long as possible, with hands free for balance, and landing on the same leg. The Crossover Hop test for distance entails three consecutive forward hops while alternately crossing over a 15 cm marked line on the floor (crossing the line medially) before landing on the same leg. After verbal instruction and practice, participants will perform three valid hop trials per leg, starting with the uninjured side. Trials are considered valid with a stable landing; attempts with balance loss or compensatory steps are repeated. The best distance (toe-to-heel) is recorded for analysis. Participants who have an isokinetic concentric knee extension torque LSI of < 70%, feel insecure about it, or have not reached the rehabilitation stage in which plyometrics are practiced will be excluded from hop-testing.

#### Time to return to sports rates

A Return to Sports Questionnaire (Table 2), adapted from the Oslo Sports Trauma Research Center (OSTRC) Overuse Injury Questionnaire [53], will be used to evaluate participants' return to sport or physical activity at various time points during the follow-up period, as outlined in Table 1.

Participants will first be asked whether they have returned to the same sport or physical activity they engaged in prior to their injury. Those who indicate that they have returned, will further be asked to specify their level of participation, according to the first question of the OSTRC questionnaire (Table 2). For participants who have not returned to their previous activity, an additional question not belonging to the OSTRC exploring the primary reasons for non-returning to sports will be asked. Options that will be included are undergoing rehabilitation, experiencing poor knee function, lacking confidence or trust in the knee, fear of reinjury, or other reasons, with space provided for elaboration.

**Table 2 Tab2:**
[figure not shown]
Return to sport questionnaire

The data collected will be used to assess return-to-sport rates, levels of participation, and factors influencing the decision not to return. This information is critical for identifying areas where additional support or targeted interventions may help optimize outcomes for individuals recovering from knee injuries.

#### Graft failure, revision ACL-R and other adverse events

Participants will be followed longitudinally for a period of 10 years to monitor ACL graft failure (recurrent instability requiring revision), ACL re-rupture rates, and other adverse event affecting outcome (contralateral ACL rupture, infection or septic arthritis, bleeding, and any reoperation performed during the study period). Clinical and surgical records will be reviewed, and participants will be contacted periodically according to Table 1 to assess their knee health and report any additional surgeries or injuries. This long-term follow-up aims to evaluate the durability of ACL-R and identify factors associated with graft failure and re-rupture, such as patient demographics, activity levels, or surgical techniques. At the 5- and 10-year follow-ups, any undocumented events will be retrospectively collected via the Swedish National Knee Ligament Register (SNKLR).

#### Imaging

Participants will undergo imagining assessment after ACL-R. Participants will undergo MRI (Magnetic resonance imaging) scans at 9 months postoperatively to assess graft Maturity. MRI will be performed with 1.5-T with standard oblique coronal proton density-weighted projection with 3 mm slices as previously described by Ma et al. [54]. Signal-to-noise quotient (SNQ) values will be measured in coronal oblique projections to visualize the entire graph. The maturity of the graft will be measured in three parts of interest: (1) the proximal part, (2) the middle part, and (3) the distal part, as described by Ma et al. [54]. Also, customary coronal, sagittal and axial projections will be done to evaluate other anatomical and operative factors. MRI will be performed at 9 months postoperatively to assess the graft maturity at the time to usual RTS evaluation.

To assess the development of OA 10 years after ACL-R, all participants will undergo bilateral knee weight-bearing radiographs. Radiographs will be obtained in standardized weight-bearing projections, including anterior–posterior and lateral views, as well as a skyline Merchant view of the patellofemoral joint, to comprehensively evaluate joint space narrowing, osteophyte formation, subchondral sclerosis, and other radiographic features of OA. Grading will be performed using the Kellgren-Lawrence classification system, a widely recognized method for assessing the severity of OA [55].

#### Statistical analysis

The statistical analysis will be conducted using SPSS software (version 29.0 or updated version). Descriptive statistics, including frequency, mean, and standard deviation, will be computed for all variables, and normal distributions will be assessed using histograms, Q-Q plots and Kolmogrov-Smirinov test. Continuous variables will be compared using parametric or non-parametric methods, depending on data distribution. Categorical variables will be analysed using Pearson’s chi-square test or Fisher’s exact test.

For anterior knee laxity measurements (KT-1000), mean ± standard deviation and median (range) values will be reported. A variance-based statistical test will be used to compare, preoperative and postoperative anterior knee laxity, as well as ATT reduction between treatment groups. The choice of test will be determined based on the distribution and characteristics of the data after collection. Adjustments for baseline values may be included as part of a secondary analysis to ensure robust comparisons.

Postoperative STS values in knee laxity will be categorized and presented in three groups according to the IKDC form: Normal ≤ 2 mm (A), nearly normal 3–5 mm (B), and abnormal > 5 mm (C and D) [10, 11, 56]. The postoperative side-to-side (STS) difference will be dichotomized as either normal (≤ 5 mm) or failure (> 5 mm). Distributions and proportions of failures will be compared between intervention groups using Pearson’s chi-square test.

The study will employ both intention-to-treat (ITT), and per-protocol (PP) to ensure robust assessment of outcomes for each surgical group. The ITT analysis will include all randomized patients in their originally assigned groups, regardless of any protocol deviations or dropouts. Missing data for the ITT analysis will be managed using imputation methods where necessary. The PP analysis will include only those patients who fully adhered to the study protocol, completing their assigned surgery and primary outcome assessments.

Secondary outcomes will be evaluated across follow-up timepoints (Table 1). Continuous outcomes will be analyzed using a variance-based statistical test to assess within-group changes over time. Adjustments for baseline values may be included as part of a secondary analysis to ensure robust comparisons. Individual time points will be assessed using independent samples t-tests or non-parametric test, depending on the distribution of the data.

Categorical outcomes will be analyzed using Pearson’s chi-square or Fisher’s exact tests. Logistic regression may also be used to adjust for potential confounders when analyzing binary outcomes. Time-to-event outcomes, such as graft failure and return to sport, will be analyzed using Kaplan–Meier survival curves and Cox proportional hazards regression models, assuming the proportional hazards assumption is met.

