### Sample size calculation

To ensure adequate power, the sample size is based on Capio Artro Clinic’s clinical registry database from KT-1000 anterior knee laxity measurements available at the time of study planning, which indicated a standard deviation (SD) of 2.3 mm. This database includes over 7000 ACL-R and has served as the source to study postoperative knee laxity, functional test and graft comparisons [10–12, 30–32]. The power analysis is structured as follows: a 5% significance level, 80% power, and a minimum detectable difference of 1 mm in KT-1000 anterior knee laxity measurements. Based on these parameters, a minimum of 85 participants per group will be required as adequate sample. To account for potential dropouts, the sample size will be increased by 15%, resulting in 100 participants per group or 200 in total [33]. Recruitment will continue until each group has 100 fully evaluable participants for primary outcome measures.

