### Randomization

In this single-center study, we will employ a simple 1:1 randomization to allocate participants to the two groups. The randomization process will be conducted by the independent researcher (not involved in the study) using randomizer.org, an online platform that generates random assignments. Participants will be randomized roughly one week after the patients sign the study consent form to participate in the study. Once included and randomized, the participants will fill out the baseline preoperative PROMs questionnaires. Given the inherently different graft harvesting sites, blinding of study participants, orthopedic surgeons as well as physiotherapist is not considered feasible. Participants will be informed of their allocation on the day of surgery, unless they explicitly requested to receive this information earlier. This approach was chosen to minimize potential cross-overs or withdrawals.

Although no stratification for sex will be performed, our aim is to have a balanced representation of sex that reflects the typical patient population for this condition at the clinic, with a distribution of 40% females and 60% males across both groups. This ratio also considers known differences in re-rupture risk and subjective outcome scores between sexes. Simple randomization in a RCT with 200 or more participants is well-suited as the likelihood of significant treatment imbalance is often negligible at these sample sizes [34]. All randomization procedures and study design elements are structured in accordance with CONSORT guidelines to ensure the highest standards of methodological transparency and rigor. Figure 1 shows the planned CONSORT flowchart.

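### The primary KT-1000 test is left open until the data are in, with both 6-month laxity and its reduction as targets and baseline adjustment optional; a pre-specified ANCOVA would close these choices and gain precision at no cost

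*Protocol article*

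**What the plan says.** All of this is in the protocol article.

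- **Test.** The Statistical analysis section assigns KT-1000 laxity an unnamed variance-based test and adds: "The choice of test will be determined based on the distribution and characteristics of the data after collection". Distribution is to be judged by histograms, Q-Q plots and a Kolmogorov-Smirnov test.
- **Measure.** That test is to compare preoperative laxity, postoperative laxity and reduction in translation between the groups. The Abstract defines the primary outcome as the side-to-side (STS) difference at 6 months. The Primary outcome section adds a parenthesis about measurement from before to after surgery, so both value and change can be read as the target.
- **Adjustment.** "Adjustments for baseline values may be included as part of a secondary analysis to ensure robust comparisons". The Discussion adds covariate adjustment only if baseline imbalance is seen. The Primary outcome section schedules KT-1000 both preoperatively and at 6 months.
- **Secondary continuous outcomes.** "Continuous outcomes will be analyzed using a variance-based statistical test to assess within-group changes over time". Single time points get independent-samples t-tests or a non-parametric test.
- **Sample size.** The calculation uses "a 5% significance level, 80% power, and a minimum detectable difference of 1 mm" and a registry value, "which indicated a standard deviation (SD) of 2.3 mm". It arrives at 85 per group, raised to 100 per group for dropout.

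**The concern.** This is a stated decision to settle the primary analysis once the data exist, not a detail passed silently to a SAP. Three things are open together: which test, which measure (6-month value or reduction), and whether to adjust for baseline. The sample size targets a mean difference of 1 mm, but no analysis is tied to that target.

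Two things are at stake. The nominal 5% level is guaranteed only if the choice among these analyses does not depend on their results, and the text gives no rule that ensures this. Power also depends on the choice. Ignoring the preoperative measurement gives up precision, and an unadjusted test of reduction can be much weaker than the test that the sample size assumed. The protocol hypothesises no difference in laxity, so a low-powered choice would lean towards the expected conclusion.

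For repeated secondary outcomes, the hypotheses on strength, hop tests and patient-reported scores concern differences between grafts, whereas the over-time analysis is aimed at change within each graft group.

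**Working it through.** **Inputs from the document.** Difference 1 mm, SD 2.3 mm, 5% level and 80% power (Sample size calculation); 1:1 allocation (Randomization). Sidedness is not stated. Two-sided is assumed, because one-sided needs only 66 per group and two-sided matches the stated figure.

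**Assumptions.** The pre-post correlation r is not given, so a range is shown. The document does not say whether 2.3 mm is the SD of the 6-month value or of the change; it is taken as the SD at each time point.

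**Step 1: reproduce the plan's figure.**
- Normal approximation: n = 2 × (1.96 + 0.84)² × 2.3² / 1² ≈ 83.0, so 84 per group.
- Exact t-test: 84.01, so 85 per group.
- Dropout: 85 / (1 − 0.15) = 100.

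The stated 85 and 100 are reproduced.

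**Step 2: power by choice of analysis.** ANCOVA residual SD = 2.3 × √(1 − r²). Change-score SD = 2.3 × √(2(1 − r)). Power is from the two-sided two-sample t-test for 1 mm.

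| r | ANCOVA SD (mm) | ANCOVA power, 85 / 100 per group | Change SD (mm) | Unadjusted change power, 85 / 100 per group |
|---|---|---|---|---|
| 0 | 2.30 | 80.5% / 86.4% | 3.25 | 51% / 58% |
| 0.1 | 2.29 | 80.9% / 86.8% | 3.09 | 56% / 63% |
| 0.2 | 2.25 | 82.0% / 87.8% | 2.91 | 61% / 68% |
| 0.3 | 2.19 | 84.0% / 89.4% | 2.72 | 66% / 73% |
| 0.4 | 2.11 | 86.8% / 91.6% | 2.52 | 73% / 80% |
| 0.5 | 1.99 | 90.2% / 94.2% | 2.30 | 80.5% / 86.4% |

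The ANCOVA entry at r = 0 is also the power of the unadjusted comparison of 6-month values. ANCOVA removes a share r² of the variance: 4% at r = 0.2 and 25% at r = 0.5. The unadjusted change score matches the unadjusted 6-month comparison only when r reaches 0.5, since 2(1 − 0.5) = 1.

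**Step 3: false-positive rate.** Simulation with no true difference: 85 per group, 4,000 runs per scenario, normal and skewed data rounded to 0.5 mm, r from 0.1 to 0.5. The Monte Carlo standard error is about 0.35 percentage points, rising to about 0.5 for rates near 12%.

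| Way of choosing | False-positive rate |
|---|---|
| Pre-specified ANCOVA | 4.6-5.2% |
| Kolmogorov-Smirnov check, then t-test or Mann-Whitney | 4.8-5.4% |
| Better of t-test and Mann-Whitney on the 6-month value | 5.8-7.2% |
| Better of 6-month and change-score t-tests | 8.4-9.9% |
| Best of both tests on both measures | 9.9-11.9% |
| The same, with ANCOVA added | 10.1-12.3% |

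A separate null simulation of 20,000 runs, taking the smallest p-value among t-test, rank test and ANCOVA on the 6-month value, gave 6.8-7.7%. The freedom to move between 6-month value and reduction does more harm than the freedom to switch tests.

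**Step 4: secondary outcomes, sentence against sentence.** The over-time sentence names within-group change. The single-time-point sentence names two-sample tests, which compare grafts. No group-by-time contrast appears, and the option to adjust for baseline is repeated as secondary.

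**The case against.** **The plan does not say it will choose by p-value.** It says the choice follows the distribution and characteristics of the data. A reader might infer that looking at the data first inflates the error rate as a matter of course. The documents do not support that: a strict normality-gated switch stays near 5%. Nor does the document say that the distribution check would be done by arm or by an unblinded analyst; it says only that participants, surgeons and physiotherapists are unblinded. This stands, so the 7-12% must be read as a worst case. It does not remove the openness of measure and adjustment, for which no rule is given.

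**The unadjusted comparison is valid.** In a randomised trial it is unbiased, and it matches the sample size calculation. The protocol intends to recruit until 100 per group are evaluable, where unadjusted power is already 86.4%, and for r up to 0.3 ANCOVA adds at most 3 points (89.4% against 86.4%). This stands: the adjustment is an improvement, not the repair of an invalid test.

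**Results in mm will exist whichever test is used.** Means with SD and medians with range are to be reported for KT-1000. This stands, although a rank test's p-value would still not refer to the 1 mm mean difference.

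**Secondary outcomes are compared between grafts.** A reader might infer from the within-group sentence that they are not. That is wrong: independent-samples tests are planned at individual time points, and the section also plans chi-square or Fisher tests, logistic regression, Kaplan-Meier curves and Cox models. Only the over-time analysis lacks a between-graft contrast.

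**Conclusion.** The point holds in a limited form. The protocol expressly postpones the choice of primary test, leaves 6-month laxity and reduction both in play, and makes baseline adjustment optional. A distribution-based switch of test alone is close to harmless; selective use of all the open choices could take the error rate to roughly 7-12%, which the plan does not propose.

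The gain from ANCOVA is modest at low correlation and material at 0.4-0.5, and its size rests on a correlation that the document does not give. The larger power risk is an unadjusted test of reduction: about 51-66% at 85 per group for r of 0-0.3, if 2.3 mm is the SD at each time point. If 2.3 mm is instead the SD of the change, that shortfall does not follow.

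The sample size is not in error. For continuous secondary outcomes, the defect is confined to the over-time analysis and to reliance on separate tests per visit with optional baseline adjustment.

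**What to change.** Before any comparison by arm, state the following.

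1. **Primary estimand:** the between-graft difference in mean STS laxity at 6 months.
2. **Primary analysis:** a linear model (ANCOVA) of 6-month STS on graft and preoperative STS, reporting the adjusted difference in mm with a 95% confidence interval. Use robust standard errors or a bootstrap if residuals are skewed. Drop the Kolmogorov-Smirnov check as a gate for the primary test.
3. **Supporting analyses:** rank tests as sensitivity analyses, and reduction in translation as a sensitivity or secondary analysis.
4. **Repeated continuous secondary outcomes:** one mixed model per outcome with baseline, graft, visit and graft by visit, reporting the between-graft difference at each visit. Treat within-group change as descriptive.

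The cost is wording in the analysis plan. SPSS, the named software, fits both models, and preoperative KT-1000 is already scheduled, so no new data are needed. The Trial status section reports 170 participants recruited and expects completion for the 6-month analysis in the second half of 2026 or early 2027, which leaves time to make the change.

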### Primary outcome

#### Knee Laxity at 6 months post ACL-R

Knee Laxity will be measured preoperatively and at 6 months postoperatively using the KT-1000 arthrometer® (MEDmetric®, Corp, San Diego, CA, USA) in accordance with the clinic’s standard routine for postoperative evaluation of ACL-R [10]. Patients will be positioned supine with the knee at approximately 20 degrees of flexion with the help of a bolster placed under the thighs, and with the feet are supported on a footrest to minimize muscle contraction and prevent external rotation. The contralateral (uninjured) knee will be tested first, followed by the ACL-injured knee. For each knee, three trials will be conducted using the standardized anterior force corresponding to 134 N (third audible “click” of the KT-1000). Between trials, the arthrometer will be recalibrated and the median value of the three valid measurements will be recorded for each side. The STS difference in ATT between the ACL-injured knee and the healthy contralateral knee (measured preoperative to postoperative) will be expressed in millimeters. To reduce inter-rater variability, all measurements will be performed by two unblinded, experienced physiotherapists, each with over 10 years of experience in arthrometric laxity assessment following ACL injury and reconstruction.

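### The three ordered IKDC laxity classes are compared with Pearson's chi-square, which ignores their order and costs about 10 points of power in a supporting analysis (minor)

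*Protocol article*

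**What the plan says.** All of this is in the protocol article. Three consecutive sentences under Statistical analysis deal with classified laxity:

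- The three-class rule, attributed to the IKDC form: "Normal ≤ 2 mm (A), nearly normal 3–5 mm (B), and abnormal > 5 mm (C and D".
- A two-class rule for the same postoperative difference, which "will be dichotomized as either normal (≤ 5 mm) or failure (> 5 mm".
- The test: "Distributions and proportions of failures will be compared between intervention groups using Pearson’s chi-square test".

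The same section gives a general rule: "Categorical variables will be analysed using Pearson’s chi-square test or Fisher’s exact test". No trend, rank or ordinal method is named for the classes.

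Under Knee Laxity at 6 months post ACL-R, "the median value of the three valid measurements will be recorded for each side", and the side-to-side difference "will be expressed in millimeters". Neither place states a reading resolution or a rounding rule.

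The Sample size calculation rests on the continuous measurement: registry data "which indicated a standard deviation (SD) of 2.3 mm", and "a 5% significance level, 80% power, and a minimum detectable difference of 1 mm in KT-1000 anterior knee laxity measurements". It arrives at 85 per group, raised to 100.

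**The concern.** Classes A, B and C/D form an ordered scale. A graft that leaves knees looser should move patients from A towards B and from B towards C/D. Pearson's chi-square on the 2 × 3 table gives the same result however the columns are arranged, so it spends a second degree of freedom on patterns that a shift in laxity would not produce. The stake is power in the clinical presentation of the primary measurement: a real shift is more likely to be reported as no difference between the classes.

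Two details of wording sit beside this. The printed bounds of A and B do not meet, so a value above 2 and below 3 mm has no class unless such values cannot occur. And a knee at 4 mm is nearly normal under the first rule but normal under the second, so a reported share of normal knees is ambiguous unless its cut-off is printed with it.

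**Working it through.** **Inputs.** From the Sample size calculation: SD 2.3 mm, difference 1 mm, 5% significance level (taken as two-sided), 80% power, 100 per arm. From Statistical analysis: cut-offs at 2 and 5 mm. Assumed, because the article gives no means: normally distributed differences, lower-group mean 1 to 2.5 mm and the other group 1 mm higher; for the class gap, means of 1 to 3 mm.

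**Step 1: the plan's own figure.** n per group = 2 × (1.96 + 0.84)² × 2.3² / 1² ≈ 83, or 84 when the unrounded value is rounded up. The t-test version needs 84.01, hence 85. Then 85 / 0.85 = 100. The stated figures reproduce. The mean comparison has about 87% power at 100 per group.

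**Step 2: one case by formula.** Take whole-millimetre readings (class edges at 2.5 and 5.5 on the underlying scale) and means of 2 and 3 mm.

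- Class shares are p₁ = (0.586, 0.350, 0.064) and p₂ = (0.414, 0.448, 0.139), with average q = (0.500, 0.399, 0.1015).
- Pearson noncentrality: 100 × Σ[(p₁−q)² + (p₂−q)²]/q = 200 × (0.086²/0.500 + 0.049²/0.399 + 0.0375²/0.1015) ≈ 6.9, on 2 df (critical value 5.99). Power is about 65%.
- Trend noncentrality, scores 0, 1, 2: mean scores 0.478 and 0.726, difference 0.248, pooled variance 0.805 − 0.602² ≈ 0.443. This gives 0.248² / (0.443 × 2/100) ≈ 6.9, on 1 df (critical value 3.84). Power is about 75%.

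The two noncentralities are almost equal. Nearly all the signal is in the ordered component, and the second degree of freedom adds only cost.

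**Step 3: simulation across assumed means** (40,000 tables per row, 100 per arm, 1 mm shift).

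| Lower mean (mm) | Whole mm: Pearson | Whole mm: trend | Continuous, cut at 2 and 5: Pearson | Continuous: trend |
|---|---|---|---|---|
| 1.0 | 58% | 69% | 62% | 73% |
| 1.5 | 62% | 73% | 65% | 75% |
| 2.0 | 65% | 76% | 67% | 77% |
| 2.5 | 68% | 77% | 69% | 78% |

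The Wilcoxon test on the classes is within about one point of the trend test. All rows lie within about 58–70% for Pearson and 69–80% for trend, and the gap is about 9–11 points throughout.

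**Step 4: values without a class.** On a continuous scale the share is Φ((3−μ)/2.3) − Φ((2−μ)/2.3). At μ = 1 it is 0.808 − 0.668 = 0.140; it is 0.168 at μ = 2 and 0.172 at μ = 2.5. That is 14–17 patients per 100. On a 0.5 mm grid only the reading 2.5 is affected: 7.0–8.7%, or about 7–9 per 100. With whole-millimetre readings it is 0: the median of three readings is one of those readings, and the difference of two whole-number medians is a whole number.

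**Step 5: the two uses of normal.** At mean 2 mm on a 0.5 mm grid, P(X < 2.25) = 54% are normal by the first rule, or 63% if 2.5 is placed in A. By the second rule P(X < 5.25) = 92% are. The boundary above 5 mm is the same in both rules, so the failure count is identical.

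**The case against.** The best reply is that this is preference rather than error. Pearson's chi-square is a valid test for a 2 × 3 table. The three classes are described as categorized and presented, and the sentence naming the test follows the binary split, for which Pearson is the ordinary choice. The trial is sized on a mean difference, which keeps its power whatever happens to the classes.

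Most of this stands as a limit on severity. It does not remove the point. The word distributions, placed alongside proportions of failures, most naturally covers the three classes. Even on the narrower reading, the general rule for categorical variables offers only Pearson or Fisher. An order-respecting test is available at almost no cost.

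On the class gap, the objection is stronger. The integer bounds fit whole-millimetre readings, and recording a median rather than a mean creates no fractions, so possibly nobody is left out. A condensed article may also leave resolution to the full protocol.

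A reader might infer more than the document supports:

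- That some patients will certainly be unclassified. This depends on a resolution the article does not state, and the range starts at zero.
- That an unblinded team will place those patients after seeing the data. Participants, surgeons and the measuring physiotherapists are described as unblinded; nothing is said about who classifies or analyses the values.
- That this is the only categorical comparison of laxity. The failure split is compared too, and there Pearson is suitable.
- That the conflicting label changes results. It affects the reported share of normal knees and not the number of failures.

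**Conclusion.** The point holds as a minor one. Comparing the three ordered classes with Pearson's chi-square gives up about 10 points of power, from about 69–80% to about 58–70%, for the protocol's own 1 mm difference at 100 per arm. This rests on the stated SD of 2.3 mm, a normal model, a pure shift between grafts and assumed lower-group means of 1 to 2.5 mm. It also takes the test sentence to include the three classes. The test is inefficient here, not wrong.

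The bounds and the label are matters of wording. The first has a consequence only if readings are finer than whole millimetres; the second needs no assumption. Neither touches the primary mean comparison, the sample size or the failure count.

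**What to change.** 1. Compare the three classes with a linear-by-linear (trend) test, a Wilcoxon test or a proportional-odds model, and name one of them before the 6-month analysis. Keep Pearson or Fisher for the binary rate above 5 mm. The downside is that an order-respecting test is less sensitive to non-monotone differences, such as one graft having more patients in both outer classes.
2. Write the classes contiguously within the stated cut-offs (A ≤ 2 mm; B > 2 to ≤ 5 mm; C/D > 5 mm), or state the reading resolution and any rounding applied before classification.
3. Rename the group at or below 5 mm *no laxity failure*, so that *normal* keeps its class A meaning.

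The cost is a few sentences and no new data. Trial status reports 170 recruited and primary completion for the 6-month analysis in the second half of 2026 or the beginning of 2027, so the change can be made before that analysis.
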